### Randomization and blindness

At the end of the baseline assessment, participants are randomized to the MBSR or the health promotion program intervention. The randomization list was generated through a website (http://www.randomization.com) in blocks of 10 participants with a ratio of 1:1 to receive the MBSR or the health promotion program (i.e., five individuals randomly allocated to each group). The allocation list is masked from all study personnel. The condition of each participant is described in different excel sheets in a way that the researcher responsible for the randomization would only have access to the allocation of the next participant (allocation concealment). Assessors and participants are blinded to the conditions prior to randomization. During the intervention, although participants know which activity they are included in, they do not know which the experimental or control conditions are. If participants want to know about our hypotheses, they may be disclosed after the study is completed. To test participants’ blinding, they fill out a questionnaire of credibility and expectancy adapted from Devilly and Borkovec [73]. Due to the researchers’ availability, the intervention facilitator and the data analyst are not blinded for participants’ conditions since it is performed by the first author of this study ([name]).

### Statistical analyses

Regarding statistical analyses, data will be explored for missing and impossible values and descriptive statistics will be provided. The analyzes will be based on the modified intention-to-treat (mITT) population (i.e., participants that participated in at least three group-sessions and have at least one post-intervention assessment). We chose three sessions based on previous studies showing cognitive changes after three sessions of cognitive training [74]. A level of significance of less than 5% will be used in the analyses.

We will use mixed-effect regression models with maximum likelihood estimation to analyze change in cognitive scores as a function of the interaction group*time and participants will be treated as a random effect. *P*-value will be set at *p* < .05. Effect sizes (Hedges, *g*) will be calculated for each score [75–77]. Demographic factors, such as gender and educational level, the number of attended sessions, as well as the score differences in stress relief, depression, anxiety, mindfulness state, and sleep quality will be analyzed by running separate models for each factor.

Concerning the interview, it will be recorded in audio and transcribed in Portuguese by a member of the research team. The interview data will be analyzed according to Malterud’s principles of systematic text condensation and guidelines for qualitative research [78]. Content analysis can be conducted using the software package NVivo 12 [79].

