**Methods:**

MEDITAGING is a two-arm randomized, double-blinded, controlled study, which will include older Portuguese-speaking migrants (*n* = 90). Participants are randomized to the MBSR or a health promotion program. Both interventions are conducted in groups over a total of 8 weeks, incorporating weekly meetings, an additional 4-hour class, and extra at-home tasks. The health promotion program has the same structure as the MBSR but comprises different activities related to dementia prevention, healthy habits, cognitive stimulation, sleeping, nutrition, watercolor painting, and physical activity. The assessment of executive functioning, physiological stress measures, self-reported questionnaires, and qualitative interviews are conducted at baseline, after 8 weeks (post-intervention), and at a follow-up session (from one to 3 months thereafter). Analyzes will be conducted using a modified intention-to-treat approach (all participants with at least 3 days of participation in the group-sessions and one post-intervention observation).

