### Adherence and feasibility

A previous study has shown a dropout rate of 5% [51]. However, the dropout rate may be higher in the MEDITAGING project since 25.2% of the Portuguese immigrants plan to commute between Portugal and Luxembourg [66]. The adherence of home practice in a previous review has shown to be around 60% [67]. To increase adherence, weekly feedback will be requested from participants throughout the intervention, in order to detect and resolve any situation that needs attention.

Due to the under-researched target population of the MEDITAGING study, it has a secondary aim of investigating the operational feasibility of the MBSR for older migrants, as well as the financial, physical, and psychological feasibility of participating in the program. In particular, the following aspects will be evaluated: if participants both, those remaining in the study and those lost to follow-up, report [1] the need of any adjustment in the program [2]; any difficulties encountered (e.g., time restriction, physical limitation, anxiety, financial problems).

For the adherence and dropout rate analysis, the proportion of participants who completed the baseline assessment and went to the first group session and the number of participants that attended at least three sessions will be considered.

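### The only stated analysis set excludes randomised participants who attended fewer than three sessions, so the group-by-time comparison is between attenders rather than between the arms as randomised

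*Protocol article*

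**What the plan says.** Under Statistical analyses, the article names one population, a modified intention-to-treat set: "participants that participated in at least three group-sessions and have at least one post-intervention assessment". The Methods part of the abstract gives the same two conditions in slightly different words: "all participants with at least 3 days of participation in the group-sessions and one post-intervention observation". The reason given for the threshold is exposure: "We chose three sessions based on previous studies showing cognitive changes after three sessions of cognitive training".

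On timing, Randomization and blindness states: "At the end of the baseline assessment, participants are randomized to the MBSR or the health promotion program intervention". After that, "although participants know which activity they are included in, they do not know which the experimental or control conditions are". The same section says that "the intervention facilitator and the data analyst are not blinded for participants’ conditions".

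The planned analysis uses "mixed-effect regression models with maximum likelihood estimation to analyze change in cognitive scores as a function of the interaction group*time", with participants as a random effect. The Background calls the trial a superiority trial and names the number of attended lessons as a factor in mindfulness gains. Outcome measures and Statistical analyses both list the number of attended sessions among the moderators to be examined.

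**The concern.** An intention-to-treat comparison is protected by randomisation because membership of the analysis set is settled before the programmes can act. Here it is settled afterwards, by whether a person came to three sessions of a programme whose content they knew. The two programmes differ in content from the first session, so those who reach three sessions need not be the same kind of people in each arm. The article also expects attendance to bear on benefit, so the filter selects on a variable that its authors believe is related to the outcome.

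Two things are at stake. First, the group-by-time effect no longer estimates the effect of being allocated to mindfulness-based stress reduction (MBSR) rather than to the health promotion programme. It compares those who stayed in one with those who stayed in the other. Second, someone who attended one or two sessions and returned for T2 or T3 is removed although the scores exist. The planned maximum-likelihood model can use such records and does not need the restriction.

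The two conditions do not weigh the same. Requiring at least one post-intervention assessment removes only people with baseline data, who add little to a group-by-time estimate. That condition is minor; the three-session rule is the point.

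**Working it through.** **1. Order of events.** Baseline, then randomisation, then session 1 onwards, then T2 immediately after the last session, then T3 one to three months later. The three-session condition is met or failed after allocation is known.

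**2. The plan's own sample size.** Inputs from Sample size estimation: f = 0.14, power 80%, type I error 5%, repeated-measures ANOVA with within-between interaction, attrition 5%, N = 90. The number of time points m and the correlation ρ are not stated; I assume m = 3 (T1 to T3) and ρ = 0.5.

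- Noncentrality λ = f²·N·m/(1−ρ), with df1 = m−1 and df2 = (N−2)(m−1) for two groups.
- N = 84: λ = 0.0196 × 84 × 3/0.5 = 9.88, df = 2 and 164, power 0.803.
- 84/0.95 = 88.4, so 89, and 90 for equal arms.

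The stated 90 is reproduced. The point does not rest on it, but it fixes the model for step 4.

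**3. Bias when there is no true effect.** Let p be the proportion of an arm excluded and s the amount, in SD of change, by which excluded people change less than retained people. With mean change set to zero in the whole arm, (1−p)·R + p·(R−s) = 0, so the retained mean is R = p·s. The spurious difference between arms A and B is p_A·s_A − p_B·s_B. With a common s this is (p_A − p_B)·s.

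The document gives no exclusion rates by arm, so all values below are assumed. The type I error is for a two-arm z-test on change with SD 1 and 45 randomised per arm.

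| Excluded A v B | s | Spurious difference | Type I error |
|---|---|---|---|
| 10% v 10% | 0.5 in both | 0 | 0.050 |
| 15% v 5% | 0.5 in both | 0.10 × 0.5 = 0.05 SD | 0.056 |
| 25% v 5% | 0.5 in both | 0.20 × 0.5 = 0.10 SD | 0.072 |
| 25% v 5% | 0.8 in both | 0.20 × 0.8 = 0.16 SD | 0.107 |

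Equal rates do not guarantee safety: if the arms lose opposite kinds of people (10% each, s = 0.5 in one and −0.5 in the other), the difference is 0.05 + 0.05 = 0.10 SD.

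**4. Power under each analysis set.** Same model as step 2. The restricted set keeps f = 0.14 with N reduced. The full set keeps N = 90, has complete outcomes, and assumes that non-attenders gain nothing, so f becomes 0.14 × (1−d).

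| Non-attenders d | Restricted set | All 90 analysed |
|---|---|---|
| 10% | N = 81: 0.79 | f = 0.126: 0.74 |
| 20% | N = 72: 0.73 | f = 0.112: 0.63 |
| 25% | N = 67: 0.70 | f = 0.105: 0.57 |

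The restricted set has the higher nominal power, but for an effect in a selected subset.

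**The case against.** The rule is pre-specified, openly labelled as modified, and given a reason. An article condenses a fuller protocol, so the absence of an all-randomised sensitivity analysis from it proves nothing. That stands, and no such absence is held against the plan. But the article itself fixes the main population, and a dose argument justifies a supportive set, not the main set of a superiority trial.

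The programmes were matched for duration, home practice, a four-hour class and a psychoeducational component, and one facilitator leads the sessions of both. The reasons for loss that the article gives, travel and sickness, are not tied to an arm. This stands in part: differential exclusion is possible, not shown.

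A reader might go further in four ways that the document does not support:

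- **That the silent retreat against the watercolour workshop drives the selection.** Both are the half-day class between sessions 6 and 7, so they can hardly explain failure to reach three sessions.
- **That any trait related to both attendance and score biases the result.** The planned effect is change over time. A stable trait equally correlated with T1 and T2 cancels; the exclusion must be related to change.
- **That a quarter of participants will be excluded.** The article says that "the dropout rate may be higher in the MEDITAGING project since 25.2% of the Portuguese immigrants plan to commute between Portugal and Luxembourg". That is a share of people with travel plans, not a dropout or exclusion rate.
- **That the rule costs power which the fix would restore.** Step 4 shows the reverse if non-attenders gain nothing, and people with no post-test reduce power under any analysis set.

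Nor does the document say whether low attenders are assessed at T2 and T3, so the amount of data discarded is unknown.

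**Conclusion.** The concern holds for the three-session rule. Followed as written, it makes the main comparison one of self-selected attenders and drops any outcome scores from those below the threshold. That the rule conditions on a post-randomisation event follows from the document alone. The size of the resulting bias does not: it needs exclusion that is related to change in score and that differs between arms in rate or in type of leaver. Over the assumed range in step 3 it runs from 0 to 0.16 SD, in either direction. It cannot be claimed that the result will be biased, or that it will favour MBSR. The case for change rests on what is being estimated and on keeping observed data. The unblinded analyst is a further reason for an inclusion rule that does not depend on attendance.

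**What to change.** - Make the primary set all randomised participants, analysed in the allocated arm whatever number of sessions they attended.
- Fit the planned maximum-likelihood mixed model to all observed T1, T2 and T3 scores.
- Invite everyone to the T2 and T3 visits already scheduled, regardless of attendance. This is the urgent part, since missed assessments cannot be recovered later.
- Keep the three-session set as a labelled supportive analysis. Use one definition in the abstract and the main text, and say whether the half-day class counts.
- Report exclusions by arm.

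The cost is a change of wording plus contact with people who stopped attending. The real downside is dilution. Under the assumptions of step 4, power with all 90 analysed is about 0.74, 0.63 or 0.57 at 10%, 20% or 25% non-attenders. Holding 80% would need 104 participants at 10% and 148 at 25%, with complete outcomes. The sponsor should state this openly. If non-attenders gain something, the loss is smaller.

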### Participants

Participants are 55 years older and over, community-dwelling, Portuguese-speaking immigrants, living in Luxembourg or frontier regions. According to our eligibility criteria (see Table 1), participants have no major neurological or psychiatric disorders or current unstable illness. Moreover, as we previously verified that Portuguese older adults often present symptoms of anxiety, depression, pain, and sleep disorders [46, 47], we opted for broader inclusion criteria to maximize ecological validity. Additionally, we believe that participants presenting these symptoms would most likely benefit from the interventions [48]. Therefore, we did not exclude participants with corresponding symptoms. The decision to use the age of participants starting at 55 was supported by the evidence that much of the cognitive decline observed in old adults already starts at middle age [49], so we expected that individuals from this age group could benefit from our interventions to preserve cognitive functioning. Additionally, we only included Portuguese-speaking participants as they represent the largest (more than a third) and most vulnerable group of immigrants in Luxembourg [7].

**Table 1 Tab1:** Eligibility criteria

Inclusion	Exclusion

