- Being a Portuguese-speaking migrant, residing in the Grand-Duchy of Luxembourg or the Greater Region; - Age: 55 years old or older; - Mastery of spoken, written, and reading Portuguese; - Subjects without cognitive impairment - verified through the MMSE, cut-off of < 22 adopted since most participants are expected to have a low education level (Kochhann et al., 2010). - Full capacity of consent.	- Previous (up to 3 years before) or current weekly participation in meditation, yoga, or mindfulness-based interventions; - Concomitant participation in another kind of group interventions (e.g., cognitive training, psychological therapy); - Attendance in psychological consultation; - Severe hearing or visual impairment (not corrected); - Severe medical condition requiring intensive medical care that makes it difficult to participate in the group sessions. - Refusal to sign the informed consent; - Diagnosis of dementia; - Clinical neurodegenerative illness, psychotic disorder, unstable psychiatric condition which makes it difficult to participate in group work, posttraumatic stress disorder or history of trauma, acute psychosis, mania, suicidality, or substance abuse within the last 6 months (cutoff: 2 points at the Adult DSM-5 Self-Rated Level 1 Cross-Cutting Symptom Measure).

*DSM-5* Diagnostic and Statistical Manual of Mental Disorders, Fifth Edition, *MMSE* The Mini Mental State Examination

Another important aspect observed among older Portuguese immigrants is language barrier, as the Portuguese often is the only language, they are proficient in or comfortable to use. As a result, it can negatively influence their social relationships, feelings of belonging, and wellbeing [50]. Social participation in which individuals interact in their mother language can lead to an increase in social integration and has been shown to contribute to a healthier aging [50]. Therefore, the MEDITAGING offers the courses in Portuguese.

Regarding the scores on cognitive functioning, we exclude participants with Mini Mental State Examination (MMSE) below 22 because it is necessary to have a considerable level of insight to take advantage of the programs. Likewise, illiterate participants are excluded as reading and writing are indispensable to carry out the activities proposed in either one of the two groups.

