### Outcome measures

As outcome variables, we will assess executive functioning as primary outcome, as well as general cognitive ability, sleep quality, perceived stress, depression, anxiety, mindfulness-trait, cortisol level, and heart rate variability (HRV) as secondary ones. Additional exploratory analyses will be done to verify if the effects are moderated by demographic factors, such as gender and educational level, as well as number of attended sessions, stress, depression, mindfulness trait, anxiety, cortisol level, and sleep quality. We anticipate that the MBSR group will present gains (post-intervention compared to baseline) in cognitive tasks and stress relief and these gains will be higher than in the control group (health promotion program). A summary of the outcome measures is provided in Table 4. We aimed to select brief measures to minimize participant fatigue.

**Table 4 Tab4:** Summary of primary and secondary outcomes

Outcome	Construct/surrogate	Description

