***Screening***		
Sociodemographic and health-related information	Sociodemographic and health-related information	It is a structured interview in which participants answered questions regarding age, gender, years of formal education, country of origin, number of years living in Luxembourg, mother language, marital status, professional occupation, people living in the household, disease history, surgical interventions, pharmacological treatments, health complaints, difficulties in daily life, psychological intervention, mindfulness or meditative practices, religion, physical exercise, weight, and height.
DSM-5 Self-Rated Level 1 Cross-Cutting Symptom (Bastiaens & Galus, 2018)	Assessment of psychopathology	The DSM-5 is a screening tool to assess various forms of psychopathology, including depression, anger, mania, anxiety, somatic symptoms, suicidal ideation, psychosis, sleep disturbances, memory issues, repetitive thoughts and behaviors, dissociation, personality functioning, and substance use. For this specific protocol, we have chosen to focus solely on items related to the domains of mania, suicidal ideation, psychosis, and substance use. Each item is evaluated using a 5-point scale, where 0 represents the absence of symptoms or no occurrence, 1 indicates mild or infrequent symptoms occurring for less than 2 days, 2 denotes mild symptoms experienced over several days, 3 signifies moderate symptoms occurring on more than half of the days, and 4 indicates severe symptoms experienced nearly every day. A rating of 2 or higher is considered a potential indicator for further investigation. However, for substance use and suicidal ideation, a rating of 1 is used as the cutoff point for considering additional inquiry.

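### The primary mixed model compares changes from baseline; conditioning on the T1 score, with age and education prespecified beside it, would be more precise on the same data

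*Protocol article*

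**What the plan says.** The Statistical analyses section gives the primary model for the cognitive scores: mixed-effects regression by maximum likelihood that will "analyze change in cognitive scores as a function of the interaction group*time and participants will be treated as a random effect". No baseline covariate is named. Table 2 schedules the TMT, Stroop and letter-number sequencing at T1, T2 and T3.

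Background variables appear only in further models. The list begins "Demographic factors, such as gender and educational level, the number of attended sessions", and these "will be analyzed by running separate models for each factor". The Outcome measures section gives the purpose, which is exploratory: to see "if the effects are moderated by demographic factors, such as gender and educational level". Age is not named in either place.

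Both variables are in the database: Table 4 (Screening) records that "participants answered questions regarding age, gender, years of formal education". The article links both to cognition. The lower age limit rests on evidence that "much of the cognitive decline observed in old adults already starts at middle age". The MMSE limit in Table 1 is a "cut-off of < 22 adopted since most participants are expected to have a low education level".

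The Sample size estimation section powers the same group-by-time interaction: f = 0.14, 80% power, 5% type I error, 5% attrition, 90 participants.

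**The concern.** A group*time model with free baseline means estimates the treatment effect as change in one arm minus change in the other. Taking a difference subtracts the whole T1 score. When a single test score is noisy, that adds the T1 measurement error to the comparison. Regressing on T1 subtracts only the part of it that predicts the later score.

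The authors say in the Discussion that the study may lack power and that differences between the arms may be small, and under Adherence and feasibility that dropout may exceed 5%. Precision obtainable from data already collected is therefore worth having. It also matters when the choice is made: under Randomization and blindness the data analyst is not blinded, so a baseline adjustment chosen after outcomes are seen would be open to challenge.

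**Working it through.** **Inputs.** From the article: three visits, two arms, f = 0.14, 80% power, alpha 0.05, 5% attrition, N = 90. Assumed, because not given: test-retest correlation rho of 0.5 or 0.7, equal variance at each visit (set to 1), equal correlation between visits, and a share R2 of score variance explained by age and education of 0.10, 0.20 or 0.35, the same at each visit.

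**1. The plan's own figure.** For the within-between interaction, lambda = f² × N × m/(1 − rho), with df1 = (k − 1)(m − 1) and df2 = (N − k)(m − 1). With k = 2, m = 3, rho = 0.5 and no sphericity correction, N = 84: lambda = 0.0196 × 84 × 3/0.5 = 9.88 on 2 and 164 df, power 0.803. Then 84/0.95 = 88.4, so 89, or 90 for equal arms. The figure reproduces. It does not fix rho, since two measurements with rho = 0.6 also give 84.

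**2. Variance of the stated contrast.** Per participant, Var(T2 − T1) = 2(1 − rho): 1.00 at rho 0.5 and 0.60 at rho 0.7. With 43 per arm (90 less 5%, rounded to 86), the standard error is √(1.00 × 2/43) = 0.2157 or √(0.60 × 2/43) = 0.1671.

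**3. Age and education as main effects in the stated model.** Stable differences between persons already cancel from the contrast in step 2.
- Complete data: the variance ratio with and without the covariates is 1.0000 at every rho tried, with 20% to 60% of between-person variance explained.
- 150 simulated maximum-likelihood fits (86 participants, three visits, rho 0.5, 40% explained): mean standard error 0.2124 both ways, with identical estimates. Only the group main effect, which is the baseline difference, became more precise (0.213 to 0.190).
- Missing visits: with 25% missing at T3 and 10% at T2, the gain is at most 1.6%.
- Covariate-by-time terms: if the covariates do not predict change, the standard error rises slightly, from 0.2124 to 0.2128.

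**4. Conditioning on T1.** The residual variance of T2 given T1 is 1 − rho². The ratio to step 2 is (1 − rho²)/[2(1 − rho)] = (1 + rho)/2.
- rho 0.5: 0.750/1.00 = 0.75, a 25% reduction.
- rho 0.7: 0.510/0.60 = 0.85, a 15% reduction.

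A common-baseline constrained model gave the same ratios, 0.750 and 0.850.

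**5. Age and education on top of T1.** The residual correlation is r = (rho − R2)/(1 − R2), and the residual variance is (1 − R2)(1 − r²).

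| rho | R2 | r | Residual variance | Further cut beyond T1 | Total cut against step 2 |
|---|---|---|---|---|---|
| 0.5 | 0.10 | 0.444 | 0.722 | 3.7% | 27.8% |
| 0.5 | 0.20 | 0.375 | 0.688 | 8.3% | 31.3% |
| 0.5 | 0.35 | 0.231 | 0.615 | 17.9% | 38.5% |
| 0.7 | 0.10 | 0.667 | 0.500 | 2.0% | 16.7% |
| 0.7 | 0.20 | 0.625 | 0.488 | 4.4% | 18.8% |
| 0.7 | 0.35 | 0.538 | 0.462 | 9.5% | 23.1% |

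In the common-baseline model, with R2 defined instead as 20% to 60% of between-person variance, the covariates add 3% to 14%, which is the same order.

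**6. In participants.** Conditioning on T1 makes 90 participants worth 90/0.75 = 120 at rho 0.5, or 90/0.85 = 106 at rho 0.7. At R2 = 0.20 the covariates alone are worth about 90 × 0.083 = 7.5 participants at rho 0.5, or 90 × 0.044 = 4 at rho 0.7.

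**The case against.** The strongest reply is that nothing here is wrong. An unadjusted group*time comparison in a randomised trial is valid, it is the contrast the trial was powered on, and no stratification factor is stated that the model would have to carry. A covariate list is also something a condensed article may leave to an analysis plan, and that plan is not shown. All of this stands, and it limits the point to efficiency. But the article does more than stay silent: it states a primary model, and a more precise model is available for the same data.

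A reader might infer that the stated model loses precision because it leaves out age and education. The documents do not support that. In that model the two variables as main effects do essentially nothing for group*time (step 3). The article's remarks concern level of cognition, and for education specifically the MMSE, a secondary outcome. They do not say that age or education predicts change over eight weeks, or the T2 score once T1 is known.

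A reader might also infer that both variables are planned as moderators. Only gender and educational level are named among the demographic factors; age is not.

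A third inference is that adjustment would repair missing data. That would need dropout to depend on age or education, whereas the reasons the article anticipates are travel and sickness.

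Finally, the sizes rest on assumed values. Most of this population has low schooling, and illiterate people and those with an MMSE below 22 are excluded. A narrowed range of education argues against the upper R2 values.

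**Conclusion.** The point holds as an improvement in efficiency. The stated model estimates a difference in change from baseline. Conditioning on T1 would lower the variance of the post-intervention contrast by about 15% (rho 0.7) to 25% (rho 0.5). Age and years of education would then add about 2% to 18%, for a total of roughly 17% to 38%. Across the assumed range, T1 supplies most of the gain and the covariates the smaller part. The figures depend on assumed correlations of 0.5 to 0.7 and assumed R2 of 0.10 to 0.35, and on equal variances and correlations across visits. The article provides none of these. It would be wrong to conclude that the planned analysis is biased or invalid, or that adding age and education to it unchanged would help.

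**What to change.** Before any outcome data are seen, specify for TMT, Stroop and letter-number sequencing a mixed model of the T2 and T3 scores with:

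- group, time and group*time;
- the T1 score of the same test as a covariate;
- age and years of education, both continuous, as fixed effects;
- participant as a random effect, as now.

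The treatment effects are then the adjusted differences between arms at T2 and T3. A common-baseline constrained model, with T1 kept as an outcome, equal T1 means in both arms and the same two covariates, is an acceptable alternative. Its equal-means assumption follows from randomisation, but is no longer guaranteed once the modified intention-to-treat rule excludes participants by attendance. Keep the moderator models separate and labelled exploratory.

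The cost is a short rewording of the primary model and a few degrees of freedom. No new data are needed. T1 is measured before randomisation, and the analysis set already requires a post-intervention assessment, so the T2 and T3 model should lose no one except a participant whose T1 score on that test is missing.
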